## Abstract

**Background:**

Sedentary lifestyles are now becoming a major concern for governments of developed and developing countries with physical inactivity related to increased all-cause mortality, lower quality of life, and increased risk of obesity, diabetes, hypertension and many other chronic diseases. The powerful onboard computing capacity of smartphones, along with the unique relationship individuals have with their mobile phones, suggests that mobile devices have the potential to influence behavior. However, no previous trials have been conducted using smartphone technology to promote physical activity. This project has the potential to provide robust evidence in this area of innovation. The aim of this study is to evaluate the effectiveness of a smartphone application as an intervention to promote physical activity in primary care.

**Methods/design:**

A two-group, parallel randomized controlled trial (RCT) with a main outcome measure of mean difference in daily step count between baseline and follow up over eight weeks. A minimum of 80 active android smartphone users over 16 years of age who are able to undertake moderate physical activity are randomly assigned to the intervention group (n = 40) or to a control group (n = 40) for an eight week period. After randomization, all participants will complete a baseline period of one week during which a baseline mean daily step count will be established. The intervention group will be instructed in the usability features of the smartphone application, will be encouraged to try to achieve 10,000 steps per day as an exercise goal and will be given an exercise promotion leaflet. The control group will be encouraged to try to walk an additional 30 minutes per day along with their normal activity (the equivalent of 10,000 steps) as an exercise goal and will be given an exercise promotion leaflet. The primary outcome is mean difference in daily step count between baseline and follow-up. Secondary outcomes are systolic and diastolic blood pressure, resting heart rate, mental health score using HADS and quality of life score using Euroqol. Randomization and allocation to the intervention and groups will be carried out by an independent researcher, ensuring the allocation sequence is concealed from the study researchers until the interventions are assigned. The primary analysis is based on mean daily step count, comparing the mean difference in daily step count between the baseline and the trial periods in the intervention and control groups at follow up.

**Trial registration:**

Current Controlled Trials ISRCTN99944116

## Background

Sedentary and physically inactive lifestyles are now becoming a major concern for governments of developed, and indeed, developing countries worldwide. Physical inactivity has been related to increased all-cause mortality, to lower quality of life, and to a higher risk of obesity, diabetes, hypertension, coronary heart disease, osteoporosis, fractures, colon cancer, breast cancer, prostate cancer, psychiatric disorders and an overall higher risk of hospitalization [1]. While the pathological effects and reductions in quality of life are of concern, so too are the associated economic costs for health services already working at capacity. According to the World Health Organisation, obesity rates have doubled since 1980 [2] and in addition, physical activity rates have fallen [3]. Of all types of physical activity, walking is the most commonly encouraged and most commonly reported form of leisure physical activity [4]. Evidence suggests that there are several requirements to successfully promote an increase in physical activity. Biofeedback is required on activity rates such as might be provided by a pedometer, realistic goal setting is required and lastly there must be motivation to undertake this change in behavior [4-6]. The powerful on-board computing ability of the smartphone has the ability to meet these requirements, with live feedback on activity measured as a step count as well as the ability to goal-set and provide a system of rewards for goals achieved. This system of live feedback is based on the use of accelerometers. Accelerometers are small single or uniaxial devices commonly found in all smartphones as well as electronics such as the Nintendo Wii controller and iPad (for example, they are the device responsible for rotating the screen from landscape to portrait). Accelerometers are an ideal choice for evaluating variability of movement and balance providing a non-invasive, portable method of measurement [7]. Pedometers containing accelerometers are well established as an acceptable form of monitoring and have been shown to be successful in promoting physical activity [8]. The advantage of using a smartphone with accelerometer-enabled application is that no additional piece of technology (that is, the pedometer) is required and people generally carry their mobile phone devices on their persons continuously. By carrying the smartphone throughout the day, with an appropriate application installed, physical activity is recorded and displayed as a daily step count. The saturation of smartphones within the mobile market (as of February 2012, 49% of US citizens had migrated to smartphones [9]), increases the potential benefit of, and ability to disseminate, using such persuasive technologies to monitor physical activity.

As far as the authors are aware after a systematic review of the literature [10], no previous trials have been conducted using a smartphone application to promote physical activity in any setting. Despite the rapid penetration of smartphones into the market place and the ready availability of multiple applications promoting physical activity, and indeed other health related outcomes, there remains little evidence for the effectiveness of such technologies. The results of a number of ongoing RCTs in the use of smart phone applications to promote health outcomes including the current trial, should begin to build an evidence base around the use of smartphone applications in the promotion of physical activity and the improvement of health related outcomes generally.

## Methods/design

### Setting

The study is taking place in the West of Ireland with recruitment in the community by the North Clare Primary Care Team (PCT). This is a rural based primary healthcare organization involving three family medicine centers and a population of approximately 8,000 patients. The study is coordinated by the Discipline of General Practice at the National University of Ireland, Galway, collaborating with the National Centre for Biomedical Engineering and Science and the Health Research Board Clinical Research Facility. All data collection, including the baseline screening and follow-up tests, occur in a community setting.

### Hypothesis

The formal null hypothesis to be tested in this study is that there is no change in mean daily step count between baseline and follow-up amongst participants in the intervention and control groups. The alternative hypothesis is that the intervention group using the smartphone application will show a significant increase in mean daily step count between baseline and follow-up in comparison to the control group.

### Sample size and power calculation

The sample size required for the proposed RCT is 80 participants. The sample size is based on the following assumptions. Assuming that the mean daily step count at baseline is 4,700 steps, it is estimated that over the length of the trial, the mean step count in the control arm will reduce by 470 (a 10% reduction) and increase by 940 (a 20% improvement) amongst those receiving the intervention [11]. Using a two-sample comparison of the mean improvement between the arms, a sample size of 33 subjects per arm is required to have 80% power at the 0.05 significance level to detect a difference in the mean improvement of 1,410 between the arms, with an estimated standard deviation of the improvement in step count of 2,000. To account for dropouts or loss of patients to follow-up, the sample size will be adjusted upward from 33 to 40 per group. All analyses will be conducted according to the intention-to-treat principle.

### Participants: recruitment and eligibility

Potential participants are referred to the trial team by their primary health care professional or they can self refer. Eligible participants are invited to attend a screening meeting with two members of the research team. A research engineer ensures that the potential participant has the appropriate mobile device (Android smartphone) and the ability to use it, and will record details of the technology being used and smartphone literacy. A research nurse ensures that the potential participant can undertake moderate exercise in the form of walking and then obtains informed consent from each participant. The research nurse then conducts the screening assessment by collecting relevant baseline clinical, anthropometric and psychological data as described in Table 1. After obtaining a written informed consent, they are randomized to intervention or control. The recruitment process is anticipated to span 12 months, from August 2012 to August 2013. The flow chart in Figure 1 represents the movement of a participant through the stages of recruitment to the study.

**Table 1 T1:** Secondary outcomes: definitions and measurement techniques

**Secondary outcomes recorded at baseline and follow-up**	**Definitions and measurements**
Systolic blood pressure (SBP)	Mean difference in mean SBP between baseline and follow-up: the research nurse will be trained to measure blood pressure using the current British Hypertensive Society (BHS) guidelines. Specifically, the nurse will initially measure blood pressure in both arms, and then take the mean of three measurements from the arm with the highest initial diastolic reading. All measurements will be taken one minute apart after initial rest of five minutes. Blood pressure will be measured using an Omron I-C10 (HEM 7070) arm monitor if arm circumference is 17 inches or less or an Omron R7 (HEM 637) wrist monitor if arm circumference is greater than 17 inches. These devices have been independently validated [12].
Diastolic blood pressure (SBP)	Mean difference in mean DBP between baseline and follow-up: the research nurse will be trained to measure blood pressure using the current BHS guidelines. Specifically, the nurse will initially measure blood pressure in both arms, and then take the mean of three measurements from the arm with the highest initial diastolic reading. All measurements will be taken one minute apart after initial rest of five minutes. Blood pressure will be measured using an Omron I-C10 (HEM 7070) arm monitor if arm circumference is 17 inches or less or an Omron R7 (HEM 637) wrist monitor if arm circumference is greater than 17 inches. These devices have been independently validated [12].
Resting heart rate	Four readings will be recorded for resting heart rate from the automated devices used to measure blood pressure as described above. The first reading will be ignored and the mean resting heart rate will be calculated as mean of the last three readings.
Body mass index (BMI)	Height in cm and weight in kg will be recorded. BMI will be calculated as weight in kg/(height in cm) [2].
Psychological evaluation	a. Mental health score will be assessed using the HADS depression scale.
	b. Quality of life will be assessed using the EQ-5D and the EQ-VAS.

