### Outcomes

The primary outcome variable is step count, measured daily for a week prior to treatment assignment (that is, baseline) and subsequently for a seven week follow-up period. Seven secondary outcomes will be measured at baseline and at the end of the follow-up period, namely: systolic blood pressure; diastolic blood pressure; resting heart rate; BMI; mental health as measured by HADS score; quality of life as measured by ED-5D and EQ-VAS. Table 1 outlines the definitions and measurement techniques for each of these secondary outcomes.

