### Analysis plan

Daily step count (primary outcome variable) will be collected longitudinally as described above. All participants will also be invited back for follow-up testing (secondary outcome variables) within one week of finishing the trial. At this follow-up visit, to evaluate the effects of the trial on the secondary outcome measures, data on the same clinical, anthropometric and psychological variables measured at baseline (systolic blood pressure, diastolic blood pressure, resting heart rate, BMI, mental health as measured by HADS score, quality of life as measured by ED-5D and EQ-VAS) will be collected.

Baseline data will be compared across the two arms using suitable numerical summaries and graphical techniques. Functional data analysis techniques, using P-spline smoothers, will be used to graphically represent the eight week daily changes in step count in order to identify a suitable weekly summary statistic.

The effectiveness of the intervention will be assessed using a linear mixed model to compare the change in the primary outcome (within subjects and between treatments) when measured as the mean, median and total weekly steps while adjusting for the following covariates as appropriate: baseline step count, age, gender, socioeconomic status as measured by “medical card eligibility”, BMI, mean systolic blood pressure, mean diastolic blood pressure, mean resting heart rate, mental health as measured by HADS score, quality of life as measured by ED-5D and EQ-VAS and smartphone literacy as measured by whether the participant had activated Email on their smartphone. Those below a certain income level (for example, $238/€184 per week net income for a single person aged up to 65 years who is living alone or $261/€202 per week net income for a single person aged 66 years and over who is living alone) [18] are said to be ‘medical card eligible’ which allows access to family doctor or general practitioner (GP) services, community health services, dental services, prescription medicine costs, hospital care and a range of other benefits free of charge. Therefore, medical card eligibility provides socioeconomic data measured atan individual level. The selection of explanatory variables for inclusion in the final model will be based on a combination of clustering, tree-based methods and variable selection techniques.

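### Table 1 gives the BMI denominator in centimetres with no conversion to metres, so BMI as written is 10,000 times too small (a minor correction)

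*Protocol article*

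**What the plan says.** The BMI row of Table 1 first fixes the units of measurement: "Height in cm and weight in kg will be recorded". It then gives the derivation: "BMI will be calculated as weight in kg/(height in cm) [2]". This is the only BMI formula in the article, and no conversion to metres appears anywhere.

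BMI is used in three places:

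- The Outcomes section lists it among the seven secondary outcomes: "systolic blood pressure; diastolic blood pressure; resting heart rate; BMI; mental health as measured by HADS score", followed by the quality-of-life measures.
- The Analysis plan lists it among the covariates for the linear mixed model of step count: "socioeconomic status as measured by “medical card eligibility”, BMI, mean systolic blood pressure, mean diastolic blood pressure". It is a candidate and not a fixed term, because "The selection of explanatory variables for inclusion in the final model will be based on a combination of clustering, tree-based methods and variable selection techniques".
- The Qualitative analysis section names it as one of the characteristics used to choose interviewees.

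**The concern.** BMI is conventionally expressed in kg/m². The table meant to define the outcome puts height in centimetres in the denominator. Someone who programs the derivation as written gets numbers that are not on the BMI scale. Reported to two decimals, ordinary values near 0.0025 would all print as 0.00, and a change of one BMI unit would appear as 0.0001.

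What is at stake is the readability and correctness of the reported BMI summaries, the treatment difference in BMI, and any BMI coefficient shown from the step-count model. The article chose to state the formula, so this is a wrong statement and not a detail left to a fuller plan.

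**Working it through.** **Inputs.** Weight in kg and height in cm (Table 1). The article gives no BMI value to reproduce, so the body sizes below are assumed for illustration.

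**Formulas.** Write w for weight in kg and h for height in cm.

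- Conventional: BMI = w / (h/100)² = 10,000 × w / h².
- Table 1, with the bracketed 2 read as an exponent: w / h².
- Ratio: 10,000, whatever w and h are.

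**Numbers.**

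| Weight, height | As written, kg/cm² | Conventional, kg/m² | Ratio |
|---|---|---|---|
| 60 kg, 160 cm | 60/160² = 0.00234 | 60/1.60² = 23.4 | 10,000 |
| 70 kg, 170 cm | 70/170² = 0.00242 | 70/1.70² = 24.2 | 10,000 |
| 80 kg, 170 cm | 80/170² = 0.00277 | 80/1.70² = 27.7 | 10,000 |
| 100 kg, 180 cm | 100/180² = 0.00309 | 100/1.80² = 30.9 | 10,000 |

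**Effect on inference.** Multiplying a variable by a constant multiplies its mean differences and standard errors by that constant, so t statistics and p-values stay the same. As a covariate in a linear model, the coefficient scales by the inverse and the treatment effect does not move. Tree splits depend only on order, which is kept.

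**Check on simulated data.** One data set of 80 people, 40 per arm, all values assumed: height mean 170 cm (SD 10), BMI mean 27 (SD 4), mean weight change 0.5 kg lower in the intervention arm (SD of change 2 kg), residual SD of steps 2,000.

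| Quantity | kg/m² | kg/cm² |
|---|---|---|
| Between-arm test of BMI change | t = -2.367, p = 0.0204 | t = -2.367, p = 0.0204 |
| Treatment effect on steps, adjusted for BMI | 1,283.7 | 1,283.7 |
| BMI coefficient | 80.2 | 802,261 |

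Only the BMI coefficient changes, by the factor of 10,000.

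**Power.** The sample size rests on a difference of 1,410 steps and a standard deviation of 2,000. BMI is not an input, so the 33 per arm is untouched.

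**The case against.** The strongest case against raising this is that it is a drafting slip with no inferential consequence. The raw height and weight are kept, so nothing is lost. The planned baseline summaries would show values near 0.0025, and an analyst would notice. Nothing in the article shows that the actual derivation code contains the slip. All of that stands, and it limits the point to a minor correction. It does not make the printed definition right.

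A reader might infer three stronger things, none of which the article supports.

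- **That the quantity is not a BMI at all.** If the bracketed 2 were a citation, the formula would be kg/cm: 70/170 = 0.41. Its ratio to BMI varies with height (62.5 at 160 cm, 55.6 at 180 cm), so people could be ranked differently. Reference 2 is indeed cited elsewhere: "According to the World Health Organisation, obesity rates have doubled since 1980 [2]". A citation therefore cannot be excluded. But the mark follows directly on a bracketed denominator, in a row labelled as body mass index, where a squared term is expected. A superscript turned into a reference marker is the likelier explanation, and a lost superscript is not an error in the plan. The unit is different: centimetres is plain text and appears in both sentences of the row.
- **That participants would be misclassified against BMI cut-offs.** No eligibility criterion, sample-size input or analysis rule in the article uses one. The interviewee selection seeks a range of characteristics, and a constant factor does not disturb order.
- **That adjustment of the primary analysis is compromised.** Under a constant factor it is not, as shown above.

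**Conclusion.** The point holds as a minor error in an outcome definition. As written, and with the bracketed 2 taken as an exponent, every BMI value, BMI change and between-arm BMI difference is 10,000 times too small, and a BMI coefficient in the step-count model is 10,000 times too large. Hypothesis tests, covariate adjustment, power and the primary outcome are not affected.

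The conclusion rests on two assumptions. The first is the exponent reading. The second is that BMI enters through ordinary linear models or order-based tree methods. A clustering or selection technique that depends on the scale of unstandardised covariates would be an exception, but the article names no such technique. The covariates already come in mixed units, so such a technique would call for standardising them anyway, which would also remove the constant factor.

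**What to change.** Replace the derivation in the BMI row of Table 1 with: *BMI will be calculated as weight in kg / (height in m)², with height in m = height in cm / 100.* Use this one definition wherever BMI is reported or modelled: the secondary outcome, the candidate covariate and the interviewee characteristics. Check that the derivation code, which is not part of the article, follows it.

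The cost is one line of text and a check of the code. Height in cm and weight in kg are already collected, so no new data are needed and nothing in the design changes.

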**Figure 1 F1:**
[figure not shown]
Participant flow through recruitment process.

Eligibility for the study is determined using the following criteria:

Inclusion criteria:

participants are adults in the community with the following characteristics:

1. over the age of 16 years

2. active Android smartphone users

Exclusion criteria:

at the time of recruitment, individuals with the following characteristics are deemed ineligible to participate in the study:

1. non Android smartphone users

2. acute psychiatric illness

3. pregnant women

4. participants who cannot undertake moderate exercise

### Randomization process

The randomization process in this RCT uses random permuted blocks to ensure similar numbers of participants in the intervention and control groups.. In advance of participant recruitment, an independent researcher is responsible for generating the allocation sequence using the free computer  software program, http://www.randomization.com. The same independent researcher is responsible for assigning participants to the intervention and control groups. Thus, the allocation sequence is concealed from all study researchers until the interventions are assigned.

### Description of interventions/comparison groups

The study is a two-group, parallel randomized controlled trial. As such, following the screening visit, eligible participants are randomly assigned to the intervention and control groups in an equal ratio of 1:1. All participants have the smartphone application downloaded free of charge onto their smartphone but not made visible to the user. For the following week after the screening visit (baseline week), all participants are asked to carry their smartphone during walking hours and continue to operate at their normal physical activity levels. All participants are then contacted by SMS and mobile phone at the end of baseline week and asked to Email their baseline step count data to the research team using a ‘share data’ function within the smartphone application.

Once baseline week data collection is completed, those assigned to the intervention group are instructed on how to turn on the smartphone application display (Figure 2) and how to position the display widget on the smartphone home screen. Intervention group participants receive a short instruction by phone on the usability features of the smartphone application settings, feedback graphs (Figure 3), and continuous feedback on their daily step count. Intervention group participants are encouraged to interact with the smartphone application and are encouraged to try to achieve the physical activity goal of 10,000 steps per day. They are also issued with the Irish Heart Foundation ‘Be Active’ physical activity promotion brochure [13] by Email. Intervention group participants are then contacted after two weeks and at the end of the of the follow-up period by SMS and mobile phone, and asked to forward, using a ‘share data’ function within the smartphone application, all daily step count data up to that point. Finally they are instructed to keep their phone charged and to always carry it during walking hours.

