**Figure 3 F3:**
[figure not shown]
Chart display of daily step counts in smartphone application.

Once baseline week data collection is completed, those assigned to the control group are encouraged to try to walk an additional 30 minutes per day along with their normal activity (the equivalent of 10,000 steps) [14] as an exercise goal. They are also issued with the Irish Heart Foundation ‘Be Active’ physical activity promotion brochure [13] by post or Email. Control group participants will then be contacted after two weeks and at the end of the of the follow-up period by SMS and mobile phone and are asked to forward, using a ‘share data’ function within the smartphone application, all daily step count data up to that point. Finally they are instructed to keep their phone charged and to always carry it during walking hours.

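### Step counts for the last five of seven follow-up weeks rest on one final participant-sent transfer; a handset export at the existing visit would recover some of what is not sent

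*Protocol article*

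**What the plan says.** The transfer procedure is set out in the protocol article under Description of interventions/comparison groups. At the end of the baseline week every participant emails the baseline counts using the app's share function. After that, for the intervention arm, "Intervention group participants are then contacted after two weeks and at the end of the of the follow-up period by SMS and mobile phone". For the control arm, in the paragraph after Figure 3, "Control group participants will then be contacted after two weeks and at the end" of follow-up. At each of these contacts the participant is asked to send every daily count recorded so far, so each transfer is cumulative.

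The Outcomes section says steps are measured daily in the baseline week and "subsequently for a seven week follow-up period".

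The Analysis plan section refers back to this route for the primary outcome and then describes the visit separately: "All participants will also be invited back for follow-up testing (secondary outcome variables) within one week of finishing the trial". The data listed for the visit are the clinical, anthropometric and psychological measures taken at baseline. Step counts are not on the list.

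The sample size section raises 33 per arm to 40 for losses and commits to intention-to-treat. The Analysis plan section assumes data missing at random in a linear mixed model, with a look at missing-data patterns and a sensitivity analysis under missing not at random.

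**The concern.** The primary outcome builds up on the participant's own phone, and the team holds only what has been sent. Between the week-2 request and the final one there are five weeks with no scheduled transfer. Everything recorded in that time depends on one later request being answered from a handset that still holds the data.

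A participant who never replies to that request, or whose phone, app or stored data is gone by then, contributes at most two follow-up weeks, even if several more were recorded. Under intention-to-treat these become missing values in the primary outcome, and the model has to cover them by assumption although measurements were made. Meanwhile all participants are invited to a visit shortly after the end, where the handset could be read, but the article assigns that visit to other data.

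**Working it through.** **Inputs**
- Follow-up of seven weeks (Outcomes).
- Follow-up transfers after two weeks and at the end, both cumulative (Description of interventions/comparison groups, both arms). I take the two weeks as counted from the end of the baseline week.
- Sample size section: "a sample size of 33 subjects per arm is required to have 80% power at the 0.05 significance level". The target is a 1,410-step gap between arms in mean change, the assumed SD of that change is 2,000, and 40 per arm are recruited. Allocation is 1:1.
- Not in the article: when participants leave and how many fail to reply. Both are assumptions below.

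**1. The plan's own figure.**
n per arm = 2 × (1.960 + 0.842)² × (2,000 / 1,410)² = 2 × 7.85 × 2.012 ≈ 31.6, so 32 by the normal approximation. The two-sample t-test version gives 32.57, so 33, which matches. This assumes a two-sided test; a one-sided test would need 25 by the normal approximation. The implied loss is 1 − 33/40 = 17.5%, or 7 per arm and 14 in all. These figures are sound.

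**2. The gap.**
- Follow-up: 7 × 7 = 49 days.
- Covered by the first follow-up transfer: 2 × 7 = 14 days.
- No scheduled transfer until the end: 49 − 14 = 35 days, and 35/49 = 71%.

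**3. Possible loss with even leaving.** Assume 14 leavers, leaving times uniform over the seven weeks, and none answering the final request.
- Recorded per leaver: 7/2 = 3.5 weeks.
- Delivered per leaver: 2 × 5/7 = 1.43 weeks.
- Lost per leaver: 3.5 − 1.43 = 2.07 weeks.
- In all: 14 × 2.07 ≈ 29 participant-weeks.
- Planned: 80 × 7 = 560. Share lost: 29/560 ≈ 5%.

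Of the 29, 14 × 2/7 × 1 = 4 arise before the week-2 transfer and 14 × 5/7 × 2.5 = 25 in the five-week gap.

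**4. Range under other leaving patterns.**
- All 14 leave after week 2, evenly over days 15 to 49: on average 18 recorded days each are unsent. 14 × 18 = 252 of 80 × 49 = 3,920 person-days, or 6.4%.
- All 14 record to the last day and never send: 14 × 35 = 490 of 3,920, or 12.5%. This is the ceiling for 14 people who do send at week 2.
- Every leaver who still replies reduces these figures.

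**5. Power if only complete participants counted (t-test).**
- 33 per arm (17.5% loss): 80.5%
- 32 per arm (20%): 79.3%
- 30 per arm (25%): 76.6%
- 28 per arm (30%): 73.6%

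These are lower-end values, because the weeks that were sent still enter the mixed model.

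**The case against.** A reader might infer that anyone who leaves after week 2 takes the recorded data with them. The text does not say so. The final request covers all days to date and is not limited to people still taking part, so someone who stops in week 6 but replies can send everything. Loss requires non-response, or loss of the phone, app or data. Baseline counts are not exposed, since they are sent separately. This objection stands and limits the point to those cases.

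A second objection is that an article condenses the full protocol, which may already provide for reading the handset at the visit or at withdrawal. That is possible, and the article does not exclude it. But it is not simply silent: it gives timing, channel and function for the transfer, refers back to that route for the primary outcome, and labels the visit as secondary-outcome testing. Stating retrieval there changes a described procedure.

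Third, the loss is small and budgeted for. About 5% is a worst case for even leaving, and 33 per arm keeps 80.5% power even if the 14 leavers contribute nothing. This stands, and no sample-size figure needs to change. A dropout allowance does not, however, make it worthwhile to lose measurements already taken.

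A reader might also infer a bias towards an early novelty effect, because what remains for non-responders is their first two weeks. The documents give no time course of the effect. A mixed model with time in it also uses the later course of those observed, and missing-pattern checks and a missing-not-at-random analysis are planned. The direction of any bias is therefore unknown.

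**Conclusion.** The point holds as a cheap improvement to data collection; the plan contains no error of calculation here and no contradiction. For 35 of 49 follow-up days the primary outcome depends on one final participant-sent transfer, in both arms, and the visit as described does not serve as a backup.

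The size is about 29 of 560 participant-weeks (about 5%), if the 14 leavers implied by the sample size leave evenly and none replies. Other leaving patterns for the same 14 give 6.4%, with a ceiling of 12.5%; any replies bring all of these down. The article gives neither leaving times nor response rates, so these are illustrations. What is at stake is avoidable missing data in the primary outcome, and neither a shown bias nor a loss of power beyond the allowance.

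**What to change.** - **Analysis plan section, follow-up visit:** add that the research nurse exports the full step history held in the app from the handset of every attender, whether or not the final transfer was received.
- **Description of interventions/comparison groups, both arm paragraphs:** add that a participant who withdraws is asked, at that contact, for one last export with the share function, in the same words in both arms.

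**Cost.** About a minute at a visit that already takes place, and one request at a contact that already occurs. Enrolment had begun when the article was written, so this would be a procedural change during the trial. The visit export comes after follow-up and so cannot expose controls to app feedback during it.

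**Limits.** Recovery is partial. Some people who do not answer the final request will also miss the visit, and neither step restores data from a lost phone or a removed app.

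**Interim transfers.** I would not add requests at weeks 4 and 6. Under the same even-leaving assumption they would cut the loss to 0.93 weeks per leaver (3 × 2/7 × 1 + 1/7 × 0.5), or 14 × 0.93 ≈ 13 participant-weeks. But each request has controls use a function inside an app whose display is hidden from them at installation and whose feedback is the intervention. The article does not say what they would see, so the saving of about 16 participant-weeks (29 − 13) carries a contamination risk that the two steps above avoid.
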